**Treatment Plan**:

- Sutent be administered PO QD from days 1 to 28 (see Figure 1)

Figure 1. Treatment Schema

Determine eligibility

**↓**

| **REGISTER** | **Treatment** | Days  1-7 | 8-12 | 13-14 | 15-19 | 20-28 | 29-42 |
| --- | --- | --- | --- | --- | --- | --- | --- |
| XRT |  | X |  | X |  |  |
| Sutent | X | X | X | X | X |  |

**↓**

Additional chemotherapy (as determined by Medical Oncology)

**↓**

Maintenance Sutent (until death or progression) and appropriate follow-up

- Radiation therapy will start on day 8 and will be given to each site for ten fractions
- Fractions must be separated by at least 16 hours
- The MTD of radiation in combination with Sutent will be determined
- Doses of radiation and Sutent will increase as shown in Table 1 in order to determine the MTD of radiation in Gy and Sutent in mg
- The RPTD will be one dose level lower than the MTD. If the MTD is not reached at dose level 5, no further escalation will occur and this will be the RPTD. The RPTD will then be used for future phase II trials.
- Starting day 43, chemotherapy may be given, as determined by the treating medical oncologist.
- Two weeks after completion of any chemotherapy, maintenance Sutent in 6 week cycles (consisting of Sutent 50 mg PO QD weeks 1-4 followed by no treatment weeks 5-6) until progression or death
- If no chemotherapy is planned, maintenance Sutent (as described above) will start on day 43.

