7.3 Supportive Care

- Antiemetics will be ordered at the discretion of the attending physician.
- Mucositis/esophagitis may be ameliorated with sulcrafate or GI cocktail (e.g. Tylenol #3 suspension, bendaryl elixir, Maalox, viscous lidocaine).
- Intravenous hydration is recommended in patients with inadequate oral intake.
- Treatment-related diarrhea will be managed with high-dose loperamide. The recommended dose of loperamide is 4 mg initially (two capsules) then 2 mg after each loose stool, not to exceed 16 mg daily.

7.4 Follow-up checklist: Follow-up visits are to be done every 2 weeks for first 2 months;
 then every 3 months for 1 years; then every 6 months indefinitely

- History and Physical
- Documentation of current medications
- Adverse effect assessment
- CT scan of chest, abdomen, and pelvis (initially 4-6 weeks following completion of radiation therapy to assess response; then every 3 months for first year then every 6 months indefinitely)
- Bone scan (initially 4-6 weeks following completion of radiation therapy to assess response; then every 3 months for first year then every 6 months indefinitely). The bone scan is optional if the patient did not have any evidence of disease on the bone scan upon enrollment into the trial.
- Whole body 18-FDG PET/CT initially 3 months following completion of radiation therapy and every 3 months for the first year and every 6 months thereafter is an acceptable alternative to CT of chest, abdomen and pelvis and bone scan
- Plain X-ray and/or CT and/or MRI of bone abnormality seen on bone scan (if clinically indicated)
- MRI brain if clinically indicated
- Hematology: CBC (hemoglobin, white blood cell count, platelets) with differential
- Biochemistry: Comprehensive metabolic profile (glucose, sodium, potassium, chloride, carbon dioxide, BUN, creatinine, calcium, total bilirubin, alkaline phosphatase, AST, ALT)- (every 3 months for first 2 years then every 6 months indefinitely)
- Tumor markers, if elevated prior to treatment, are recommended
- 18-FDG PET scan every 6 months (optional).

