11. Radiation is to be delivered to each site over 10 fractions separated by at least 16 hours. Up to 5 sites may be treated. **(Added 7/27/06)** For patients with 3 to 5 sites of disease, it may be difficult to treat all sites of disease during one day. For these patients, an acceptable variant is to treat all 2 to 3 sites during days 8 to 19 and to treat the remaining sites on days 20 to 33. For these patients only, concurrent Sutent will continue until day 42.
12. Radiation Doses (Phase I): A phase I escalation of doses will be performed in order to determine in MTD in Gy

Doses of radiation will increase as follows in order to determine the MTD of radiation in combination with Sutent:

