**11. ADDITIONAL INTERVENTIONS – CHEMOTHERAPY, SURGERY AND/OR ADDITIONAL RADIATION**

11.1 Interventions prior to protocol therapy: If chemotherapy, surgery and/or radiation are recommended by the treating physicians based on the patient’s clinical needs, they may be performed two weeks before or after days 1-28 of protocol therapy.

For instance, a patient with a history of breast cancer status post mastectomy (three years ago) and adjuvant chemotherapy now presents with a solitary brain metastasis, a single lung lesion and two bone lesions. The brain metastasis and lung lesion are both amenable to resection. Subsequently, the patient receives whole brain radiation and taxane based chemotherapy. After chemotherapy, CT of the chest abdomen and pelvis and MRI of the brain reveal no evidence of metastatic disease but bone scan demonstrates residual uptake in the two bone lesions. Two weeks after completion of chemotherapy, the patient is eligible for protocol therapy. The patient will receive Sutent on days 1-28 and extracranial stereotactic radiation on days 8-12 and 15-19 as per protocol. Two weeks after protocol therapy (day 43), the patient may receive additional chemotherapy. After completion of all planned chemotherapy, the patient will start maintenance Sutent. Therefore, all of the chemotherapy, surgery and whole brain radiation are allowed by protocol but are not considered “on protocol therapy”. While all toxicities of these interventions will be documented and recorded, any toxicity resulting from non-protocol therapy will not count as dose-limiting toxicity.

11.2 If patients have documented progression during additional chemotherapy and/or maintenance Sutent, the patient will be taken off protocol. At that time, any necessary intervention (chemotherapy, surgery and/or radiation will be allowed).

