**13. MEASUREMENT OF EFFECT**

- Response and progression will be evaluated in this study using the new international criteria proposed by the RECIST Committee. (38) Changes in only the largest diameter (unidimensional measurement) of the tumor lesions are used in the RECIST criteria.
- All lesions (except lesions seen on bone scan alone) are considered to be target lesions and are measurable. They are defined as being accurately measured in one dimension (longest diameter to be recorded). All tumors must be recorded in millimeters (or decimal fractions of centimeters) using a ruler or caliper.
- Lesions seen on bone scan only are not measurable and therefore are evaluated separately
- All baseline evaluation should be performed as closely as possible to beginning of the treatment and never more than 4 weeks before the beginning of treatment.
- The same method of assessment and the same technique should be used to characterize each identified and reported lesion at baseline and during follow-up.
- First assessment should be performed 4-6 weeks after completion of radiation therapy.
- Response Criteria for all lesions (except lesions seen only on bone scan):
  - Complete response (CR): Disappearance of all lesions
  - Partial response (PR): At least 30% decrease in the sum of the longest diameter (LD) of all lesions, taking as a reference the baseline sum LD
  - Progressive disease (PD): At least a 20% increase in the sum of the LD of the target lesions, taking as a reference the smallest sum LD recorded since the treatment started or the appearance of one or more new lesions
  - Stable disease (SD): Neither sufficient shrinkage to qualify for PR or sufficient increase to qualify for PD, taking as reference the smallest LD since the treatment started.
- Response Criteria for lesions seen only on bone scan:
  - Complete response (CR): Disappearance of lesion.
  - Stable disease (SD): Persistence of lesion on bone scan.
- Evaluation of best overall response:
  - The best overall response is the best response recorded from the start of the treatment until disease progression/recurrence (taking as reference for progressive disease the smallest measurements recorded since the treatment started). The patient’s best response assignment will depend on the achievement of both measurement and confirmation criteria:

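### Non-protocol treatment may begin on day 43, before the first response scan is due, and responses that follow it still count towards the response rate at the recommended phase II dose

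*Protocol*

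**What the plan says.** **Radiation.** The synopsis Treatment Plan states: "Radiation therapy will start on day 8 and will be given to each site for ten fractions". The worked example in Section 11.1 gives the calendar: "The patient will receive Sutent on days 1-28 and extracranial stereotactic radiation on days 8-12 and 15-19 as per protocol". For patients with 3 to 5 sites, Section 8.1 accepts a variant: "treat all 2 to 3 sites during days 8 to 19 and to treat the remaining sites on days 20 to 33". It adds: "For these patients only, concurrent Sutent will continue until day 42".

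**Other treatment.** The synopsis says: "Starting day 43, chemotherapy may be given, as determined by the treating medical oncologist". Section 11.1 says of chemotherapy, surgery and radiation that "they may be performed two weeks before or after days 1-28 of protocol therapy". It classes them as permitted but outside protocol therapy and keeps their toxicity out of the DLT count.

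**Imaging.** Section 13 says: "First assessment should be performed 4-6 weeks after completion of radiation therapy". Section 7.4 times the first CT and bone scan the same way, "initially 4-6 weeks following completion of radiation therapy to assess response", but gives 3 months after radiation for PET/CT used as the alternative. Footnote 8 of the checklist table puts the first PET/CT at 4-6 weeks. Neither the weekly list in Section 7.2 nor the on-treatment columns of that table contain a scan.

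**Endpoint.** Section 1 makes response rate in patients treated at the recommended phase II dose (RPTD) a secondary phase II endpoint. Under Section 13 the window for best overall response opens with treatment and closes at progression or recurrence. Starting other anticancer treatment does not close it.

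**The concern.** The RPTD is a dose level of radiation plus Sutent, so a response rate in patients given it will be read as the activity of that combination. If other anticancer treatment can begin before the first response scan, and the response window stays open afterwards, some counted responses may come from that treatment. Section 11.1 also allows surgery after days 1-28. Section 13 defines complete response by lesions no longer being present and does not exclude lesions that were cut out.

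The distortion runs one way, towards more apparent activity, and there is no control arm to reveal it. The protocol separates toxicity of non-protocol treatment from that of the combination, but it draws no such line for response.

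**Working it through.** **Inputs.** Last radiation day: 19 on the standard schedule (Section 11.1), 33 in the variant (Section 8.1). Concurrent Sutent ends on day 28, or day 42 in the variant. First scan: 4-6 weeks, that is 28-42 days, after radiation (Sections 7.4 and 13). Alternative PET/CT date: 3 months, taken here as 90-92 days (Section 7.4).

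**The plan's own figure.** Two weeks free after day 28 gives 28 + 14 + 1 = day 43, which matches the synopsis and Section 11.1.

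**Scan day** = last radiation day + interval. **Lag** = scan day - first day on which non-protocol treatment may start.

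- Standard: 19 + 28 = 47 and 19 + 42 = 61.
- Variant: 33 + 28 = 61 and 33 + 42 = 75.
- In the variant, day 43 follows from the synopsis and from days 1-28 in Section 11.1. If the same gap is counted from the end of Sutent, the day is 42 + 14 + 1 = 57. The documents do not settle which applies.
- PET/CT at 3 months: 19 + 90 to 19 + 92 = days 109-111; in the variant, 33 + 90 to 33 + 92 = days 123-125.

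| Schedule | First scan (day) | Other treatment from (day) | Lag (days) |
| --- | --- | --- | --- |
| Standard, 4-6 weeks | 47-61 | 43 | 4-18 |
| Variant, 4-6 weeks, gap from day 28 | 61-75 | 43 | 18-32 |
| Variant, 4-6 weeks, gap from day 42 | 61-75 | 57 | 4-18 |
| Standard, PET/CT at 3 months | 109-111 | 43 | 66-68 |
| Variant, PET/CT at 3 months, gap from day 28 | 123-125 | 43 | 80-82 |
| Variant, PET/CT at 3 months, gap from day 42 | 123-125 | 57 | 66-68 |

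If footnote 8 governs PET/CT, its rows become the 4-6 week rows. Every lag is positive. A 4-week scan could fall by day 42 only if radiation ended by day 42 - 28 = day 14, and neither schedule does that.

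**Confirmation.** Section 13 requires CR or PR to be confirmed at least 16 weeks (112 days) after criteria are first met. The earliest confirmation of a response first seen on day 47 is 47 + 112 = day 159, well after other treatment may have begun.

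**The case against.** The strongest reply is that the protocol studies a sequence. Further chemotherapy is a box in the Section 3 schema between concurrent treatment and maintenance Sutent. The stated phase II goal is what adding radiation and Sutent achieves, and the Section 16 benchmark is chemotherapy alone. Response under the whole sequence is a coherent quantity, and how later therapy is handled in analysis is often left to an SAP. This stands: the timing is a design choice and not a contradiction. What remains is that Section 13 fixes the response window and Section 1 ties the result to the RPTD, so the rate needs a label saying what it measures.

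A reader might infer more than the documents support:

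- *That any shrinkage after chemotherapy counts.* It does not. PR needs at least a 30% fall in summed longest diameters, CR and PR need the 16-week confirmation, and Appendix 3 adds independent review of every CR and PR. None of these steps asks which treatment caused the change.
- *That the first scan is heavily contaminated.* On the standard schedule exposure by then is at most 4-18 days and may matter little. Later scans, which also feed best response, are more exposed.
- *That the longest lags are the schedule.* The 18-32 day and PET/CT figures each depend on one of two readings that the text leaves open.
- *That primary PFS is biased in the same way.* PFS is set against chemotherapy alone, so later chemotherapy is less of a problem there. The point concerns response.
- *That a scan should be required after day 28 and before any other treatment.* In the variant, radiation runs to day 33, so such a scan could precede its completion. Scanning only those going on to other treatment earlier would also give them a different progression schedule, which feeds PFS.

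**Conclusion.** The point holds in a limited form. No scheduled post-baseline scan is certain to precede non-protocol treatment. In patients who receive such treatment, responses meeting the CR or PR criteria are credited to patients at the RPTD whatever produced them.

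The number of responses affected cannot be computed, because the protocol does not state how many patients will have chemotherapy, surgery or radiation afterwards. If none do, the effect is nil. In a patient who has none, the first scan reflects protocol treatment only, including the first days of maintenance Sutent on the standard schedule. Nothing obliges the oncologist to start on day 43, so the lags give the longest possible exposure at the first scan under each reading. The resection route is permitted by Section 11.1, although its only worked example places surgery before protocol therapy.

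This is a correctable weakness in the definition of one secondary endpoint. It does not undermine the phase II design.

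**What to change.** **Sections 13 and 16.** Report the response rate in two parts over the same denominator: responses whose criteria were first met before the first non-protocol anticancer treatment, and responses first met after it. Attribute only the first part to radiation plus Sutent, and describe the total as the rate for the whole sequence. State that a lesion removed by surgery or ablation counts neither as gone for CR nor as shrinkage for PR.

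**Timing.** The protocol team should reconcile the first-scan dates in the checklist table, Section 7.4 and Section 13 (including the two PET/CT dates) with the day-43 start in the synopsis and Section 11.1, and say how the two-week gap runs in the multi-site variant. Any response scan should stay after completion of protocol radiation, and the progression assessment schedule should be the same for all patients.

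**Cost.** The response changes need only wording and the start date of any non-protocol treatment. The attributable rate may look lower: on the present schedule a patient who starts chemotherapy on day 43 cannot have a response first recorded at a scheduled scan before it. The split also leaves one limit in place, since confirmation 16 weeks later may still be obtained on other treatment.

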**4.** **INCLUSION CRITERIA**

1. Histologically or cytologically confirmed diagnosis of cancer (including epithelial carcinoma, sarcoma, and melanoma)
2. Age 18 years or older
3. Life expectancy > 3 months
4. Patients with AJCC (6th edition, 2002) stage IV cancer with distant metastases and without pleural or pericardial effusion at diagnosis and before start of study
   1. Patients with pleural effusion that is transudative, cytologically negative,

and non-bloody are eligible

- 1. If a pleural effusion is too small for diagnostic thoracentesis, the patient will be eligible.

1. Patients with 1-5 sites of maximum tumor dimension (for each individual site) of ≤ 10 cm or < 500 cc volume and amenable to radiation therapy as seen on standard imaging (CT, MRI, bone scan, PET/CT)
2. Unidimensionally measurable disease (based on RECIST) is desirable but not strictly required.
3. Brain metastases must have been treated prior to enrollment on study, preferably with stereotactic radiosurgery or surgery.
4. Eastern Cooperative Oncology Group (ECOG) performance status ≤ 2 (Karnofsky ≥ 60%)
5. No prior radiation therapy to currently involved tumor sites
6. Room air saturation (SaO2) > 90%
7. Patients must have normal organ and marrow function as defined below:

Hemoglobin > 9.0 g/dl

Absolute neutrophil count (ANC)  1,500/l

Platelets  100,000/l

Total bilirubin within institutional limits

Albumin > 2.9 g/dl

Alkaline phosphatase < 2.5x upper limit of normal

AST and ALT <2.5 x upper limit of normal

1. Informed consent must be obtained from all patients prior to beginning therapy. Patients should have the ability to understand and the willingness to sign a written informed consent document.
2. Inclusion of Women and Minorities: Both men and women of all ethnic groups are eligible for this trial. The proposed study population is in the table below:

Table 2:

|  | White, not of Hispanic origin | Black, not of Hispanic origin | Hispanic | Asian or Pacific Islander | Unknown | Total |
| --- | --- | --- | --- | --- | --- | --- |
| Male | 24 | 4 | 6 | 2 | 0 | 36 |
| Female | 20 | 3 | 5 | 1 | 0 | 29 |
| Total | 44 | 7 | 11 | 3 | 0 | 65 |

1. Radiation therapy requirements: Patient must have a completed treatment plan approved by the protocol review team ([name] or [name] AND [name] or [name])

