**Table 3**

| **All Measurable Lesions** | **Lesions on bone scan only** | **New Lesions** | **Overall Response** |
| --- | --- | --- | --- |
| CR | CR | No | CR |
| CR | SD | No | PR |
| PR | SD | No | PR |
| SD | Any | No | SD |
| PD | Any | Yes or No | PD |
| Any | Any | Yes | PD |

CR = complete response; PD = progressive disease; PR = partial response; SD = stable disease

- Note:
  - Patients with a global deterioration of health status requiring discontinuation of treatment without objective evidence of disease progression at that time should be classified as having “symptomatic deterioration.” Every effort should be made to document the objective progression, even after discontinuation of treatment.
  - In some circumstances, it may be difficult to distinguish residual disease from normal tissue. When the evaluation of complete response depends on this determination, it is recommended that the residual lesion be investigated (fine needle aspirate/biopsy) before confirming the complete response status.
- Confirmatory Measurement/Duration of Response
  - Confirmation
    - To be assigned a status of PR or CR, changes in tumor measurements must be confirmed by repeat assessments that should be performed at least 16 weeks after the criteria for response are first met.
  - Duration of Overall Response
    - The duration of overall response is measured from the time measurement criteria are met for CR or PR (whichever is first recorded) until the first date that recurrent or progressive disease is objectively documented (taking as reference for progressive disease the smallest measurements recorded since the treatment started).
    - The duration of overall CR is measured from the time measurement criteria are first met for CR until the first date that recurrent disease is objectively documented
  - Duration of Stable Disease
    - Stable disease is measured from the start of the treatment until the criteria for progression are met, taking as reference the smallest measurements recorded since the treatment started.
- Progression-Free and Overall Survival
  - Progression-free (time to progression): From the date of registration to the date of progressive disease or death
  - Overall survival time: From the date of registration to the date of death or date of last patient contact if censored

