### 1. Source document verification of eligibility, response, and toxicity.

### 2. Regulatory review of IRB compliance and external reporting requirements.

### 3. Drug accountability and handling.

### 4. Completeness and quality of data.

## B. Response Review

Response Review is performed prior to quarterly Clinical Trials Monitoring Committee meetings on all cases exhibiting a partial response or complete response on any therapeutic clinical trial conducted at the Mount Sinai School of Medicine Department of Radiation Oncology. An independent investigator who is not a principal involved in the study, reviews and confirms measurements and source documentation.

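### Section 13 sets no lower lesion size and no minimum millimetre increase for progression, so reading error alone can create PFS events in patients with one or two small lesions

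*Protocol*

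**What the plan says.** Section 13 (Measurement of Effect) adopts RECIST by citation and then writes out its own rules.

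- Targets: "All lesions (except lesions seen on bone scan alone) are considered to be target lesions and are measurable". The next sentence adds "They are defined as being accurately measured in one dimension (longest diameter to be recorded"). No millimetre threshold is given.
- Recording: "All tumors must be recorded in millimeters (or decimal fractions of centimeters) using a ruler or caliper".
- Progression: "Progressive disease (PD): At least a 20% increase in the sum of the LD of the target lesions". The comparison is with the lowest sum measured so far on treatment, and any new lesion also counts as progression. No absolute increase is required.
- Confirmation, in the notes after Table 3: "To be assigned a status of PR or CR, changes in tumor measurements must be confirmed by repeat assessments". Nothing similar is stated for progression.
- Independent review, in Appendix 3 (Response Review), is performed "on all cases exhibiting a partial response or complete response on any therapeutic clinical trial". Progression calls are not covered.

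Eligibility sets only upper lesion sizes (10 cm or 500 cc in Section 4, 6 cm in the Eligibility Summary) and admits patients with a single site. Under Section 13, progression or death is the PFS event. Section 1 makes PFS a phase II primary objective. Under Section 11.2, documented progression during chemotherapy or maintenance takes the patient off protocol.

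**The concern.** A purely relative threshold shrinks with the lesion. When the smallest sum is one lesion of about 10 mm, 20% is 2 mm, only two steps of a scale recorded in millimetres. The reference is the smallest sum so far, so one low reading lowers the bar for every later scan. One high reading then meets the definition, with no repeat measurement or second reader required.

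The patients most exposed have one or two lesions that are small, or have become small after treatment. A false call shortens their PFS, stops the search for best response and, under Section 11.2, can take them off protocol. Against a fixed historical benchmark the error counts against the regimen.

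**Working it through.** **The plan's own figures.** Section 16 gives 87% power for a 25% increase in time to progression (6.4 to 8.0 months, SD 3.2, n = 38). As a one-sample normal test, Φ(1.6 / (3.2/√38) − 1.96) = 86.9%. It also gives 70% power for 2-year PFS of 15% against 5%. The exact rule of at least 5 of 38 gives 69.3%. Both reproduce, and neither is disputed here.

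**Threshold in millimetres.** 0.20 × sum gives 2 mm at 10 mm, 3 mm at 15 mm, 4 mm at 20 mm and 6 mm at 30 mm.

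**Two readings of one unchanged lesion.** With true size L and independent errors of standard deviation s, P(second ≥ 1.2 × first) = 1 − Φ(0.2L / (s√(1 + 1.2²))). At s = 1.0 mm the denominator is 1.562. For L = 10 mm: 1 − Φ(1.280) = 10%. For 15 mm: 1 − Φ(1.921) = 2.7%. For 20 mm: 1 − Φ(2.561) = 0.5%. Rounding to whole millimetres raises the 10 mm figure to 15%, because a recorded 12 against 10 qualifies.

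**Repeated scans with true progression competing.** The inputs were:

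- From the documents: scans 4 to 6 weeks after radiation, then every 3 months in year 1, then every 6 months. I placed seven scans at 1.8, 4.8, 7.8, 10.8, 13.8, 18 and 24 months. The true median is 8.0 months (6.4 × 1.25).
- Assumed: reading SD of 0.5, 1.0 or 1.5 mm per lesion, independent between scans; rounding to 1 mm; exponential true progression; a mixed cohort of 1 to 5 lesions of 10 to 60 mm, halved by the first scan.

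Each cell has 200,000 simulated patients. Progression is called when the sum is at least 1.2 times the running minimum, baseline included. The entries are the percentage of patients whose first event is false.

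| Scenario | As written, SD 0.5 | SD 1.0 | SD 1.5 | With 5 mm minimum, SD 1.0 | SD 1.5 |
| --- | --- | --- | --- | --- | --- |
| One lesion, 20 mm halved to 10 mm | 10 | 33 | 42 | 0.5 | 7 |
| One stable 15 mm lesion | 0.3 | 19 | 39 | 0.7 | 10 |
| Two stable 10 mm lesions | 0.7 | 21 | 40 | 8.5 | 28 |
| One stable 30 mm lesion | 0 | 0.1 | 3.5 | 0.1 | 3.5 |
| Mixed cohort | 0.8 | 3.6 | 8.6 | 0.7 | 5 |

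A single lesion stable at 10 mm lies above the others (44% at SD 1.0 and 55% at 1.5).

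**Effect on the mixed cohort.** Median PFS falls from 8.0 to 7.8 months (SD 1.0) or 7.6 (SD 1.5). 38 × 0.036 = 1.4 patients and 38 × 0.086 = 3.3 patients. 2-year PFS falls from about 12.5% to 11.1% or 9.7%.

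**Sensitivity.** With six scans instead of seven, the mixed cohort gives 3.2% and 7.6%. With seven scans but no rounding, the halved 20 mm lesion gives 26% and 39%, and the stable 15 mm lesion 14% and 36%.

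**The case against.** Four points can be made on the other side.

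**RECIST is cited, and targets must be accurately measurable.** The cited criteria may carry a size floor; they cannot be checked here. But the local sentence says that all lesions other than bone-scan-only ones are measurable, and it gives no threshold. If a floor was intended, that sentence conflicts with it; if not, there is none. The wording needs repair either way.

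**Confirming response but not progression is a legitimate choice.** This stands. It guards against overstating benefit, and the bias here is against the regimen. The missing confirmation only explains why a single noisy reading is final; it is not an error in itself.

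**The noise is assumed.** This also stands. The protocol asks for the same method and technique throughout, which should reduce error. At an SD of 0.5 mm the mixed cohort is almost untouched. The share of patients with one or two small lesions is unknown.

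**True progression comes first in most patients.** This limits the size. If true progression is ignored, the same simulation gives cumulative false calls over seven scans of 81% for the halved 20 mm lesion and 47% for the stable 15 mm lesion. A reader might take these as the expected error in the trial. The documents do not support that: Section 16 assumes a median of 6.4 months on chemotherapy and under 5% progression-free at 2 years, so few patients pass through all the scans.

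Two further inferences should not be drawn. Section 4 says "Unidimensionally measurable disease (based on RECIST) is desirable but not strictly required". That does not contradict Section 13, which names an unmeasurable class (bone scan only) and handles it separately. And although the false-call rate falls as lesion number rises, the planned Cox regressions on variables such as number of sites are exploratory and univariate, with no decision attached, so little rests on that distortion.

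**Conclusion.** The point holds as a limited but avoidable weakness in the definition of a primary endpoint. Followed literally, Section 13 turns a 10 mm to 12 mm reading into a PFS event.

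With an assumed reading SD of 1.0 to 1.5 mm and a true median of 8 months, about 20 to 40% of patients with a single small or shrunken lesion (a stable 15 mm lesion, or 20 mm halved) would have a false first event. In the illustrative mixed cohort it is about 3 to 8%, just under 9% in the least favourable run: roughly 1 to 3 of 38 patients, with median PFS shortened by about 0.2 to 0.5 months. A single 30 mm lesion at SD 1.0 mm is practically immune.

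These figures rest on the assumed SD, on errors independent between scans, and on an invented mix of lesion sizes. The direction, towards shorter PFS, does not depend on the exact values. The documents do not support reading this as a failure of the PFS endpoint for the cohort as a whole.

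**What to change.** In Section 13:

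1. Require for size-based progression both an increase of 20% or more and an absolute increase of at least 5 mm in the sum over the smallest sum on study.
2. Admit to the sum only lesions at or above a stated, reproducibly measurable baseline size (for example 10 mm longest diameter), and reconcile the sentence making all lesions measurable with the cited criteria.
3. Follow smaller lesions as non-measurable. New lesions remain progression.

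The 5 mm and 10 mm values are proposals; the documents contain neither. In the mixed cohort the 5 mm condition cuts false first events from 3.6% to 0.7% at SD 1.0 mm and from 8.6% to about 5% at SD 1.5 mm. The size floor adds nothing there because all the simulated lesions start at 10 mm or more.

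The cost is wording and a flag on the lesion form, with no extra scans. Small true growth will be called somewhat later. If reading error is larger, false progression is reduced rather than removed: two stable 10 mm lesions at SD 1.5 mm still give 28% with the 5 mm condition alone.
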